#### Iron supplementation

Starting from around the 12th week of gestation and continuing up to partum, adherence to prescription will be recorded. The dose assignments will be random and followed-up blind for each RCT stratum. The principal active ingredient is ferrimanitol ovoalbumin. The doses of 20 mg, 40 mg and 80 mg per day of elemental iron correspond to 150 mg, 300 mg and 600 mg ferrimanitol ovoalbumin. The reference dose is 40 mg/d, similar to that routinely prescribed in clinical practice [14].

#### Biological samples of the RCT

The blood extractions at visits 1, 3 and at birth, will be more than are normally taken for biological analyses in a RCT. This is because slightly larger amounts are required for subsequent analyses such as specialized biochemical measurements (ferritin, cortisol) and genetics (C282Y and H63D of the HFE gene). These samples will be treated and stored for subsequent analyses in the BioBank of the reference hospital of the participating PCCs.

#### Participant withdrawal

Participants will be free to withdraw from the trial at any time, and without the need to provide any reason. The information that may already have been collected on participants will still be used. Withdrawal from the study will not affect the standard of care received from the practice. If participants withdraw before randomization, they will be replaced by an appropriate substitute.

The pregnancies diagnosed as anemic during the RCT will have the iron supplementation from the RCT changed, and will be treated according to the standard clinical practice protocol. These women will continue forming part of the study and will have the same follow-up, except they will be considered as therapeutic failures in the intent-to-treat statistical analyses, and will not be taken into account in the protocol analysis.

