### Outcomes

#### Primary outcomes

Principal variables in the pregnancy are iron status of the mother at each clinical visit (anemia, ferropenic anemia, risk of hemoconcentration) and birth weight of the baby.

Definition of main outcome variables

– Anemia is defined as Hb <110 g/L in the 1st and 3rd trimester, Hb <105 in 2nd trimester, Hb <120 g/L post-partum [21].

– Ferropenic anemia is defined as: Hb < the normal limit, and serum ferritin (SF) <15 μg/L [22].

– Hemoconcentration risk is defined as: Hb >130 g/L in the 2nd and 3rd trimester [4].

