#### Analysis of the primary outcome

The effects of iron dose supplement in each RCT on the biochemical iron status and mother-child health will be compared using regression models adjusted for those variables that can influence the relationship. Logistic regression or Cox models will be applied for qualitative variables such as, for example, the percentage of anemia or hemoconcentration at the end of pregnancy. Linear multiple regression models will be applied for dependent quantitative variables. The models will be adjusted for those variables that biologically affect the relationships studied, such as the serum ferritin levels, presence of alterations in the HFE gene, age of the mother, gestational age, parity, anthropometric indices, diet, and lifestyle, and the interactions between these variables. Initially included in the model will be all those variables that form part of the theoretical model and, in a second phase, the variables for entry into the model will be selected step by step (forward and backward) to achieve the most reduced stable models.

Conditions for the application of models will be verified using standard techniques that are based, essentially, on residuals analysis. The bilateral null hypothesis of normality, no difference, and non-significance of the regression coefficients, will be rejected when their probabilities are <5%. The data will be analyzed using the latest version of SPSS/PC package for Windows.

Data will be analyzed in 2 ways:

a) Intention-to-treat analysis

The principle of “intention-to-treat” is a way of analyzing the results that considers all individuals entered into the study, according to the group to which they were originally assigned, although they may not have complied with the protocol. In this case, in all the circumstances that have led to not having hemoglobin determinations before delivery, we will proceed to incorporate at this time-point the immediately-prior determination of hemoglobin. All randomized participants randomized who had received at least one dose of study medication will be included.

b) Per-protocol analysis

Included in the analysis will be only those pregnant women who received the allocated intervention at randomization. The per-protocol population (PP) will include those participants who had taken at least the 80% of the study medication, with proper assessment of adherence, or without any major protocol violations.

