Pregnant women diagnosed with anemia at the start will be treated according to the usual protocol, and not as a part of the current study. Women diagnosed with anemia posteriorly, will be treated with standard therapy, but will remain part of the study in the intention-to-treat analysis. However, they will not be considered in the per-protocol analysis.

Data missing from the study variables will be treated with the direct likelihood method [34] when no data is available. In these cases, the profile of pregnant women will be used to adjust the estimates of these parameters.

An analysis of sensitivity will be performed using a mixed model based on constraint-based patterns of missing values without dependence on the future to assess the robustness of the main results of the Mixed Model Repeated Measures against the possible transgression of random default assumption.

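### The per-protocol analysis excludes women diagnosed with anemia, so membership of that set depends on a primary outcome

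*Protocol article*

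**What the plan says.** Under Participant withdrawal, the protocol article states that women diagnosed as anemic during the trial have their trial iron changed and receive standard care. It adds that "These women will continue forming part of the study and will have the same follow-up", and then that "they will be considered as therapeutic failures in the intent-to-treat statistical analyses, and will not be taken into account in the protocol analysis".

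Under Analysis of the primary outcome, the article returns to women diagnosed after the start. They "will be treated with standard therapy, but will remain part of the study in the intention-to-treat analysis", and then: "However, they will not be considered in the per-protocol analysis". Here they are retained for intention-to-treat with no mention of failure.

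Primary outcomes lists "iron status of the mother at each clinical visit (anemia, ferropenic anemia, risk of hemoconcentration") and birth weight. Ferropenic anemia is defined there as low hemoglobin together with ferritin below 15 μg/L, so every ferropenic case is also an anemia case. The Sample size section sizes Stratum 1 on iron deficiency anemia in the third trimester.

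**The concern.** A per-protocol set is meant to hold women who took the treatment as planned. Here a woman can take every dose and still be removed because she had the outcome. Three things follow.

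- For anemia and ferropenic anemia, the comparison has few or no events left, whatever the doses do.
- In Stratum 2, the second hypothesis (Background and rationale) is that hemoconcentration falls without iron deficiency appearing. A set cleared of diagnosed anemia would show almost none on 20 mg/d by construction, and could be read as confirming that claim.
- For hemoconcentration and birth weight, women are removed on an event after randomisation that the trial itself expects to differ between arms.

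The article describes only two analyses, and this is one of them. The rule is also stated twice, so it is not a detail left to an analysis plan.

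**Working it through.** **Inputs.** From Sample size: one-sided alpha 0.05, beta 0.20, drop-out 35%, a 10-point reduction, iron deficiency anemia 23.5% in Stratum 1, hemoconcentration risk 14.7% in Stratum 2. Stated sizes are 283 and 156 per group.

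**1. Reproducing the stated sizes.** Arcsine formula: n = 2(1.645 + 0.842)² / h², with h = 2·asin√p₁ − 2·asin√p₂, then divided by 1 − 0.35.

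| Stratum | p₁ vs p₂ | Evaluable n per arm | After drop-out | Stated |
|---|---|---|---|---|
| 1 | 23.5% vs 13.5% | 184 | 284 | 283 |
| 2 | 14.7% vs 4.7% | 101 | 156 | 156 |

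The planning figures are therefore understood correctly, apart from a rounding difference of one in Stratum 1.

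**2. Expected events in Stratum 1.** Evaluable women per arm: 283 × 0.65 = 183.95, about 184.

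- Higher-rate arm: 183.95 × 0.235 = 43.2, about 43 events.
- Lower-rate arm: 183.95 × 0.135 = 24.8, about 25 events.

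**3. The same comparison after the exclusion.** If every woman diagnosed with anemia is excluded, 43 vs 25 becomes 0 vs 0. The 10-point difference becomes 0, and a logistic model for this outcome cannot be estimated.

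There is a narrower reading. The Interventions section has the week-36 blood results discussed at the next visit, 40 days post-partum. If only women whose supplement was changed before delivery are excluded, cases first found in the week-36 sample stay in. The article does not give the split between earlier and week-36 cases, so their number cannot be computed. The comparison would still be restricted to women who escaped anemia earlier.

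**4. Effect on hemoconcentration (illustration).** Assume the same true rate r in both Stratum 1 arms, exclusions of 23.5% and 13.5%, and no woman with both conditions. The per-protocol rate is r / (1 − proportion excluded).

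| Assumed r | Arm losing 23.5% | Arm losing 13.5% | Spurious difference | Odds ratio |
|---|---|---|---|---|
| 5% | 6.5% | 5.8% | 0.8 points | 1.14 |
| 10% | 0.10/0.765 = 13.1% | 0.10/0.865 = 11.6% | 1.5 points | 1.15 |
| 15% | 19.6% | 17.3% | 2.3 points | 1.16 |

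The values of r are assumptions. The exclusion trigger is any anemia, whereas 23.5% and 13.5% are iron deficiency anemia, so actual exclusions could be larger. The no-overlap assumption holds at a single visit but need not hold across visits. For birth weight, the article gives no figures from which to compute a shift.

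**5. The intention-to-treat wording.** Participant withdrawal says "they will be considered as therapeutic failures in the intent-to-treat statistical analyses" without naming an outcome or a coding. Analysis of the primary outcome retains the women and does not mention failure. For the anemia outcome, failure and event are the same thing. For hemoconcentration and birth weight the article gives no coding, and birth weight has no failure value. Because follow-up is unchanged, both can be analysed as recorded.

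**The case against.** The strongest reply is that nothing is deleted from the trial: the intention-to-treat analysis is listed first and retains every anemia event. Any per-protocol set also departs from randomisation to some degree, and the illustrated distortion for hemoconcentration is modest. All of that stands. It limits the damage to one of the two analyses but does not justify selecting that analysis on its own outcome.

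The complete loss of events also depends on reading the rule as covering week-36 diagnoses. That stands too, and the size is therefore given under both readings.

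A reader might go further in two directions that the article does not support.

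- That women with anemia count as failures for every intention-to-treat outcome, so that hemoconcentration and birth weight are corrupted. The article does not say this. Any example in which the planned Stratum 2 benefit vanishes needs anemia rates that the article does not give and a coding that it does not state. What holds is that the scope of the failure rule is undefined.
- That women below 80% adherence enter the per-protocol set, because its definition ends "with proper assessment of adherence, or without any major protocol violations". The 80% condition can be read as governing the whole sentence, with the conjunction joining only the closing phrases. The wording is ambiguous and worth tidying, but it does not establish that such women are included.

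**Conclusion.** Wrong as written. The per-protocol rule makes membership depend on a primary outcome that is also the Stratum 1 sizing endpoint. On the planning figures, 43 vs 25 expected events fall to 0 vs 0, or to the week-36 cases alone on the narrower reading. This analysis therefore cannot validly test the Stratum 1 hypothesis, and an absence of anemia on 20 mg/d in its Stratum 2 results would not be evidence. The spurious hemoconcentration difference in Stratum 1 would be about 0.8 to 2.3 points for assumed true rates of 5% to 15%, with the no-overlap assumption above.

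The undefined scope of therapeutic failure in the intention-to-treat analysis is a secondary point that needs clarifying, not a demonstrated bias.

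**What to change.** - **Per-protocol set.** Define it by adherence up to the diagnosis of anemia and by major protocol violations unrelated to the outcome. Keep women diagnosed with anemia in it and count them as anemia events. Change both places that state the exclusion.
- **Therapeutic failure.** Limit it in the intention-to-treat analysis to the anemia outcome. Analyse hemoconcentration and birth weight as observed.
- **Ferropenic anemia.** Use the ferritin samples already planned. Biological samples of the RCT lists the larger draws at visits 1, 3 and birth, not at week 24, and the stored samples are assayed only at the end of the study. The plan should therefore state how a woman diagnosed at week 24 without a ferritin value is classified.
- **Per-protocol definition.** Reword the closing phrases so that the conjunction is unambiguous.

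The cost is wording only, with no new data. The downside is that the per-protocol set will include some women whose iron was changed after diagnosis, which should be disclosed with the results.

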#### Discontinuation visit

This visit will take place only in case of the participant’s withdrawal from the study at any time outside the scheduled timetable. The exact date and reason for discontinuation will be registered. If possible, the healthcare professional will assess the woman’s health status via clinical history notes, and an ultrasound. A blood sample will be solicited for routine tests. The adherence to the iron supplementation up until the discontinuation of the treatment will be recorded, as will any adverse events. All the questionnaires will be filled-in, including: FFQ; IPAQ; STAI, Fagerstrom_Q. In case of having given birth, all the variables related to delivery and the newborn will be collected and a questionnaire on post-partum depression (Edinburgh Postnatal Depression Scale; EPDS) and the Parenting Stress Index (PSI) will be applied.

### Outcomes

#### Primary outcomes

Principal variables in the pregnancy are iron status of the mother at each clinical visit (anemia, ferropenic anemia, risk of hemoconcentration) and birth weight of the baby.

Definition of main outcome variables

– Anemia is defined as Hb <110 g/L in the 1st and 3rd trimester, Hb <105 in 2nd trimester, Hb <120 g/L post-partum [21].

– Ferropenic anemia is defined as: Hb < the normal limit, and serum ferritin (SF) <15 μg/L [22].

– Hemoconcentration risk is defined as: Hb >130 g/L in the 2nd and 3rd trimester [4].

### Participant timeline

Clinical follow-up of the pregnancy in the PCC will be according to the program set by ASSIR. The participant timeline is detailed in Figure 1

– Recruitment visit (previous to week 12 of gestation)

– 1st visit of the study (around 12th gestational week)

– 2nd visit of the study (around 24th gestational week)

– 3rd visit of the study (around 36th gestational week)

– 4th visit of the study (40 days post-partum)

### Sample size

The principal variables taken into account in calculating the size of sample needed are iron deficiency anemia, risk of hemoconcentration in the third trimester of pregnancy, and birth weight of the baby.

To achieve the study’s main objective, sample size is calculated in accordance with the following parameters: an alpha risk of 0.05 and a beta risk of 0.20 in a one-tailed test of comparison. A drop-out rate of 35% is factored-in.

To calculate the sample size needed to reduce the prevalence of iron deficiency anemia and hemocentration risk by 10 points, we consulted previous data from our research group [5,6,8]. We had observed a prevalence of 23.5% of iron deficiency anemia in the 3rd trimester in pregnant women with Hb levels of 110-130 g/L in the first trimester and a prevalence of risk of hemoconcentration of 14.7% in the 3rd trimester of pregnant women who started pregnancy with Hb levels of 130–150 g/L.

We found that, in Stratum #1 of the RCT, it will be necessary to include 283 women in each group and in Stratum #2 of the RCT 156 women would be necessary in each group.

With respect to child development, to detect differences in weight of the newborn ≥200 g taking into account a standard deviation (SD) of 450 g [5], the estimation suggests that it will be necessary to have 106 women in each group.

Hence, the overall study sample is calculated as 878 women: 566 in Stratum #1 and 312 in Stratum #2.

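### The sample size rests on a one-tailed 5% test but the analysis uses a two-sided 5% test, so each stratum has about 70% power, not 80%.

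*Protocol article*

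**What the plan says.** The Sample size section of the protocol article fixes the error rates as "an alpha risk of 0.05 and a beta risk of 0.20 in a one-tailed test of comparison", and adds "A drop-out rate of 35% is factored-in". The target is to "reduce the prevalence of iron deficiency anemia and hemocentration risk by 10 points". The reference rates are "a prevalence of 23.5% of iron deficiency anemia in the 3rd trimester" for Stratum 1 and "a prevalence of risk of hemoconcentration of 14.7% in the 3rd trimester" for Stratum 2. The result, per arm, is that "it will be necessary to include 283 women in each group and in Stratum #2 of the RCT 156 women would be necessary in each"; in total, 566 + 312 = 878 women. For a birth-weight difference of 200 g with SD 450 g, the same section says "it will be necessary to have 106 women in each group".

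Under Statistical methods, the section on analysis of the primary outcome sets the rejection rule: "The bilateral null hypothesis of normality, no difference, and non-significance of the regression coefficients, will be rejected when their probabilities are <5" per cent. That is a two-sided test at 5%, and it names both the null of no difference and the regression coefficients that carry the dose comparison.

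**The concern.** A one-sided 5% test has a critical value of 1.645 and a two-sided 5% test one of 1.960. A trial sized to reach 80% power against the first falls short against the second. The article declares no one-sided primary test in its analysis section and does not otherwise explain the difference.

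A one-tailed test also sits poorly with the hypotheses in the Background. In each stratum they name both doses as possibly the more effective, depending on ferritin and HFE status, and they ask that a gain on one iron outcome should not bring a loss on the other.

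Two things are at stake. A null result would be read against a stated 80% power that the planned analysis does not have. And with two sidedness rules in one document, a p-value that passes one-sided but not two-sided could be reported either way.

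**Working it through.** **Inputs, all from the Sample size section.** One-sided alpha 0.05; power 0.80; drop-out 35%. Stratum 1: 23.5% against 13.5%. Stratum 2: 14.7% against 4.7%. Birth weight: 200 g, SD 450 g. The two-sided 5% level comes from the section on analysis of the primary outcome. Normal quantiles: 1.645 (one-sided 5%), 1.960 (two-sided 5%), 0.842 (80% power).

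**1. Reproducing the stated sizes.** Arcsine formula: n = 2(z_alpha + z_beta)² / h², with h = 2·arcsin√p1 − 2·arcsin√p2, then divided by 1 − 0.35 = 0.65. One-sided, (1.645 + 0.842)² = 6.183.

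- Stratum 1: h = 0.2597, h² = 0.06746; n = 2 × 6.183 / 0.06746 = 183.3; 183.3 / 0.65 = 282.01, rounded up to **283**.
- Stratum 2: h = 0.3499, h² = 0.12243; n = 2 × 6.183 / 0.12243 = 101.0; 101.0 / 0.65 = 155.4, rounded up to **156**.

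Both match. With the same drop-out inflation and rounding up at each step, two-sided calculations (arcsine, unpooled, pooled, continuity-corrected) give 359 to 394 and 199 to 240, so none reproduces either figure. One coincidence is worth noting: a two-sided continuity-corrected calculation with no drop-out gives 156 in Stratum 2. The same route gives 256 in Stratum 1, not 283, and ignores the stated drop-out.

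**2. Power under the two-sided test.** Evaluable women per group: 283 × 0.65 = 183.95 and 156 × 0.65 = 101.4.

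Arcsine: power = Φ(h√(n/2) − 1.960).

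- Stratum 1: 0.2597 × √91.975 = 2.491; Φ(2.491 − 1.960) = Φ(0.531) = 70.2%.
- Stratum 2: 0.3499 × √50.7 = 2.491; Φ(0.531) = 70.2%.

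Pooled chi-square: power = Φ{[(p1 − p2)√n − 1.960·√(2p̄(1 − p̄))] / √(p1(1 − p1) + p2(1 − p2))}.

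- Stratum 1 (p̄ = 0.185): (1.356 − 1.076) / 0.5446 = 0.514; Φ = 69.6%.
- Stratum 2 (p̄ = 0.097): (1.007 − 0.820) / 0.4125 = 0.452; Φ = 67.5%.

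A check that needs no event rates: a design with exactly 80% power one-sided has two-sided power Φ(1.645 + 0.842 − 1.960) = Φ(0.526) = 70.1%.

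**3. What two-sided 80% would need.** With (1.960 + 0.842)² = 7.849:

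- Stratum 1: 232.7 / 0.65 = 358.02, rounded up to 359 per group.
- Stratum 2: 128.2 / 0.65 = 197.3, rounded up to 198 per group.
- Total: 2 × (359 + 198) = 1,114 women against 878.

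With the planned evaluable numbers, the reduction detectable with 80% two-sided power is 11.2 points in each stratum (pooled formula), or 11.1 and 10.9 points (arcsine).

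**4. Birth weight.** n = 2[450(z_alpha + z_beta)/200]².

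- One-sided, as stated: 62.6 / 0.65 = 96.3, rounded up to 97.
- Two-sided: 79.5 / 0.65 = 122.3, rounded up to 123.

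Neither is 106. Both are below 156 and 283. Two-sided power for 200 g after 35% loss is 89% in Stratum 2 and 99% in Stratum 1.

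**The case against.** **The 70% assumes that every woman lost contributes nothing.** The intention-to-treat analysis keeps all randomized women who took at least one dose and carries the previous hemoglobin forward. Stratum 2's outcome depends on hemoglobin alone. If carried-forward values counted as full information, two-sided power would be 85 to 87% at 156 per group and 87% at 283. That is an upper bound. A value from an earlier visit is not third-trimester status, and Stratum 1's outcome also needs ferritin, which the carry-forward rule does not mention. The Sample size section itself budgets for 35% loss, so the power it claims has to be judged on the same basis.

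**A one-tailed test can be defended.** The target is worded as a reduction, and the hypotheses could be read as describing subgroup dependence rather than an undirected comparison. That is arguable, but the finding does not rest on it: the analysis section specifies a two-sided test, and the two sections must agree whichever is preferred.

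**The source of 106 is unknown.** A two-sided test with 25% loss gives 79.47 / 0.75 = 105.96, which rounds up to 106; a two-sided test with n × 1.35 gives 107.3. So the drop-out input may differ as well as the sidedness. This stands as an explanation of how 106 may have arisen. It does not rescue the figure, because the section states 35% loss, and 123 is what that loss and a two-sided test give.

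**Conclusion.** The contradiction is real and alters the stated power. With the two-sided 5% test that the analysis section specifies, power to detect a 10-point reduction is about 70% in Stratum 1 and 68 to 70% in Stratum 2. About 3 in 10 such comparisons would miss the planned effect, against the 2 in 10 claimed.

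These figures apply within each stratum to the binary iron outcome used to size it, not to 878 women pooled. They assume the stated reference rates, complete loss of 35% of women, and an unadjusted comparison of two proportions. The birth-weight comparison remains adequately powered; only its stated number is wrong.

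**What to change.** Keep 878 women and the two-sided 5% test. In the Sample size section:

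- Replace one-tailed with two-sided.
- State that about 184 and 101 evaluable women per group, after 35% loss, give two-sided power of about 70% (Stratum 1) and 68 to 70% (Stratum 2) for a 10-point reduction, or 80% for a reduction of about 11 points (11.2 by the pooled formula). Name the formula used.
- Correct 106 to 123 per group for birth weight, and note that it does not determine the sample size. If a different drop-out rate was intended there, say so.

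This costs only text, with no change to recruitment or visits, but the stated power becomes less favourable. Two other routes would also remove the contradiction: enlarging the trial to 1,114 women (236 more), or declaring and justifying a one-sided primary test in the analysis section. The first is expensive, and the second fits the hypotheses less well.
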